## Research objectives

The main objectives of the CHAMP trial are to examine the clinical value, cost and cost-effectiveness of the administration of CBT in health anxious patients attending out-patient clinics in secondary care. Specifically we hypothesised that (i) between 5 and 10 sessions of health anxiety directed cognitive behaviour therapy using the Salkovskis/Warwick model [11,12] would be more effective than normal care in the clinic in reducing abnormal health anxiety recorded by changes in the Health Anxiety Inventory (HAI)[13] one year after randomisation to the trial, and (ii) the cost of the CBT and control are equivalent, the endpoint for this outcome is the cost of health service interventions at 2 years adjusted for baseline values.

The secondary hypotheses are that, compared with the control condition, health anxiety directed cognitive behaviour therapy will lead to significantly greater improvement in health anxiety at 3, 6 and 24 months measured using the Health Anxiety Inventory (HAI)[13], in self-rated generalized anxiety measured using the Anxiety section of the Hospital Anxiety and Depression Rating Scale (HADS-A)[14], in quality of life using the EQ-5D measure of health-related quality of life [15], and in social functioning using the Social Functioning Questionnaire (SFQ)[16], all at 6, 12 and 24 months, result in the loss of the diagnosis of hypochondriasis at 24 months using the criteria of the Structured Clinical Interview for DSM-IV [17] and will be a cost-effective use of resources, where improvements in outcomes (measured using the HAI and in QALYs) are considered worthwhile.

In addition we will test the hypotheses that health anxiety focused cognitive behaviour therapy will be less effective in patients who have additional comorbid pathology in the form of (i) obsessional symptomatology (using the Short Obsessive Compulsive Screening (SOCS)[18]), dependent personality (using the Dependent Personality Questionnaire [19]), and hypochondriacal and other personality disorders [20] (using the Personality Assessment Schedule-Quick Version (PAS-Q)[21]) and that these comorbid disorders will be associated with increased costs.

The study also allows prevalence estimates to be made for health anxiety in different age groups and in different medical clinics.

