The remaining clinical assessments, in addition to the main health anxiety one (HAI) examined the presence of generalised anxiety and depression (measured with the HADS scale [14]) as these are common in patients with hypochondriasis, and also adversely affects quality of life (EQ-5D)[15], and social functioning (SFQ)[16]. These assessments were given at baseline and at 6m, 12m and 24m (or earlier and at intervening periods if drop-out or loss to follow-up was likely). To ensure the highest possible follow-up the intention was to contact patients after 18 months to be reminded of the 2 year assessment, and if for any reason (eg being out of the country), the final assessment might be made earlier. The HAI was also given at 3 months by post or by telephone with a research assistant. Service use data for the economic evaluation was collected using the Adult Service Use Schedule (AD-SUS), an interviewer-assessed instrument designed by one of the applicants and based on previous economic evaluations in adult mental health populations [22,23], and also by examination of computerised hospital records. AD-SUS data were recorded at baseline and at 6, 12 and 24 months. Where the AD-SUS data conflict with the data obtained from the computerised records the AD-SUS data will take precedence only when it refers to a contact at a hospital not included in the electronic data search, as the details of admission and investigations is more likely to be correct from official records than from personal retrospective recall. Data on workplace absenteeism and presenteeism [24] were also recorded at 6, 12 and 24 months follow-up. In addition the SCID-I hypochondriasis questions [17] are to be administered again at 24 months to determine if each patient still satisfies the requirements for DSM-IV hypochondriasis. All these instruments are given at face to face interview but also have the advantage that they can be given over the telephone if necessary, and this can be useful in reducing loss to follow up. All assessments are carried out by independent research assistants who have had no contact with the patient at other times and who are carefully masked to avoid disclosure of allocation (see below).

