## Statistical analysis

All primary statistical analysis will use the intention-to-treat principle. The primary endpoint will be analysed using a mixed model with time, treatment, time × treatment interaction as fixed effects, baseline measurement as covariate, and patient as random effect. The treatment difference at 12 months together with its 95% confidence interval will be derived from the mixed model.

Missing data will be treated as missing at random in the above mixed model analysis and no imputation will be made. To assess the sensitivity of the result to this assumption, the last observation carried forward (LOCF) strategy will be used to compute the missing HAI at during the follow up visits. Other assessments will be analysed in a similar way.

The primary economic evaluation will only include those for whom complete data at baseline, 12 and 24 months follow-up are available. Sensitivity analysis will then include those cases with missing data, where LOCF will be used to account for missing data. The following baseline characteristics of study participants with available and unavailable service use data will be compared: centre, gender, living arrangements, ethnicity, marital status, education, EQ-5D.

For each piece of service use information collected with the AD-SUS, a unit cost will be applied and the total costs calculated. The total cost per participant is calculated by summing all costs. All unit costs will be for the financial year 2008-2009. Costs in the second year will be discounted at a rate of 3.5%, as recommended by the National Institute for Health and Clinical Excellence [28].

The difference in mean costs between active treatment and control groups together with the 95% confidence interval will be derived. The equivalence margin is pre-specified as £150. The equivalence will be declared between active and control groups in terms of secondary economic outcome if the 95% confidence interval falls within (-£150, +£150).

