Even in situations where equivalence or non-inferiority are demonstrated, exploration of the joint distribution of costs and effects in a cost-effectiveness analysis (CEA) is recommended to represent uncertainty [29] and to help interpret the economic results. For these reasons, we propose to undertake a CEA irrespective of whether or not non-inferiority in the primary clinical outcome is demonstrated. Cost-effectiveness will be assessed using the net benefit approach [30] with reference to Bosmans' methods (31) for economic evaluations alongside equivalence or non-inferiority trials.

The cost-effectiveness analysis will use the primary outcome measure the HAI and a cost-utility analysis will be completed using QALYs derived from the EQ-5D data. A number of one-way sensitivity analyses will test the robustness of the results to the assumptions made in the economic evaluation.

The numbers (with percentages) of losses to follow-up at 12, and 24 months after randomisation will be reported and compared between the treatment arms with absolute risk differences (95% Confidence Intervals). Deaths will be reported separately for each group. The CONSORT procedure will be used for reporting flow through the trial.

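### The complete-case cost comparison states no covariates, and its missing-data comparison omits baseline service cost and baseline HAI and states no split by arm

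*Protocol article*

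**What the plan says.** All references are to the protocol article.

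- **Analysis set** (Statistical analysis): "The primary economic evaluation will only include those for whom complete data at baseline, 12 and 24 months follow-up are available".
- **Estimate** (Statistical analysis): the difference in mean costs is given with a 95% confidence interval, and equivalence is declared if that interval lies within ±£150. No covariate is named at this point.
- **Comparison of those with and without data** (Statistical analysis): "The following baseline characteristics of study participants with available and unavailable service use data will be compared", followed by the list "centre, gender, living arrangements, ethnicity, marital status, education, EQ-5D". Arm is not mentioned.
- **Sensitivity analysis** (Statistical analysis): "Sensitivity analysis will then include those cases with missing data, where LOCF will be used to account for missing data".
- **Losses** (Statistical analysis, closing paragraph): the proportions lost at 12 and 24 months are compared between arms as risk differences with confidence intervals.
- **Endpoint definition** (Research objectives): "the endpoint for this outcome is the cost of health service interventions at 2 years adjusted for baseline values".
- **Baseline data held** (Assessments): "AD-SUS data were recorded at baseline and at 6, 12 and 24 months". The HAI is the screening instrument (Target population and procedure), and its baseline value is the covariate in the primary clinical model (Statistical analysis).

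**The concern.** A complete-case difference in mean costs is biased when the patients who are missing differ in cost from those observed, and differ by an amount that is not the same in the two arms. A useful check therefore looks at variables close to cost, within each arm.

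Five of the seven listed characteristics are sociodemographic: gender, living arrangements, ethnicity, marital status and education. The other two are centre and EQ-5D. The two baseline variables that the protocol itself ties most closely to cost are absent. Baseline cost is the natural reading of the baseline adjustment promised in the Research objectives. Health anxiety is described in the Background as what drives consultation and investigation. With no split by arm, selection that cancels between arms cannot be told from selection that does not.

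At stake is the equivalence conclusion, which turns on a margin of £150. A table showing no imbalance on the seven items could be taken as support for the complete-case result when it says little about the threat that matters.

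**Working it through.** **Inputs** (Sample size and Statistical analysis): 186 completers per group; 20% drop-out by 24 months; 466 randomised and 372 completers; common SD of cost £580; margin ±£150 judged on a 95% interval.

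**1. The plan's missing share.** 186 / 0.80 = 232.5, rounded up to 233 per group, and 2 × 233 = 466. The stated total reproduces. It implies 466 − 372 = 94 participants without complete data, or 47 per arm.

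**2. Room for error in the equivalence rule.**
- SE of the difference = 580 × √(2/186) = £60.1.
- Half-width of the 95% interval = 1.96 × 60.1 = £117.9.
- To pass, the observed difference must lie within ±(150 − 117.9) = ±£32.1.

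**3. Illustrative bias.** If a share f of one arm is missing and those patients cost k SD more than that arm's completers, the completers' mean is too low by f × k × 580. The values of k are assumptions; the documents give none.

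| f | k | Shift in cost difference, selection in one arm only |
|---|---|---|
| 0.20 | 0.1 | £11.6 |
| 0.20 | 0.25 | £29 |
| 0.20 | 0.5 | £58 (58/150 = 39% of the margin) |
| 0.20 | 1.0 | £116 |
| 0.10 | 0.5 | £29 |

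If the same selection acts in both arms, the shift is £0.

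**4. What a £58 shift could do.** Suppose the true difference is £150, so the arms are not equivalent, and the shift runs towards zero. The observed difference then centres on 150 − 58 = £92. The chance of declaring equivalence is Φ((32.1 − 92)/60.1) − Φ((−32.1 − 92)/60.1) = about 14%. Without the shift it is Φ((32.1 − 150)/60.1) − Φ((−32.1 − 150)/60.1) = about 2%.

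**5. What adding the rows could show.** For 372 available against 94 unavailable, the SE of a standardised difference is √(1/372 + 1/94) = 0.115. Power at the two-sided 5% level is about 14% for a difference of 0.10, 58% for 0.25, 82% for 0.33 and 99% for 0.5. Within one arm (186 against 47) the SE is √(1/186 + 1/47) = 0.163, and power for 0.25 is about 33%. The by-arm table should therefore be read through the size of the differences, not through significance tests.

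**6. What the covariates could add in precision.** If baseline and follow-up cost correlate at r (an assumption) and £580 is the unadjusted SD, the half-width becomes 117.9 × √(1 − r²). It stays at £117.9 for r = 0 and falls to 117.9 × 0.866 = £102.1 for r = 0.5.

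**The case against.** The strongest reply has five parts.

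- **Other safeguards exist.** A reader might infer that the seven-item comparison is the only one. It is not: LOCF brings the incomplete cases back in, and loss rates are compared by arm. Each helps in part. LOCF fills gaps without describing who is missing, and puts an earlier period's cost in place of a later one. Equal loss rates can go with different kinds of patient being lost.
- **The list is not blind to cost.** A reader might infer that the comparison could never show relevant selection. EQ-5D and centre are both plausibly related to cost, so some could appear. The supportable description is that the list is poorly aimed.
- **Adjustment is already promised.** The Research objectives define the cost endpoint as adjusted for baseline values, so it would be wrong to say that the protocol intends an unadjusted comparison. However, the analysis section does not carry this through, and neither section says which baseline values are meant.
- **The article is condensed.** Table layout may be left to a fuller plan, and the text does not say that arms will be combined. This stands as regards layout. The list of variables, however, is written out in the article.
- **The size is assumed.** Nothing in the documents supports a one-arm gap of 0.5 SD. Early drop-out is reported as below 10%, though that is not 24-month loss. Service use is collected "and also by examination of computerised hospital records" as well as by interview, so a missed interview need not mean that all cost data are lost. All of this stands.

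Nor can one assume that baseline cost is known for everyone: the complete-case rule itself allows for missing baseline data.

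**Conclusion.** The point holds as a minor, nearly free improvement. The analysis section does not name the covariates for the cost difference, and its comparison of participants with and without service use data leaves out the two collected baseline variables closest to cost and states no split by arm.

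The effect on the cost difference cannot be derived from the documents. It is £0 if selection is equal in both arms, and £58 if 20% are missing with a 0.5 SD gap in one arm only. These figures illustrate how sensitive a £150 margin is. They are not the amount that the fix removes: the illustrated gap is in follow-up costs that nobody observes, and adjustment removes only the part explained by baseline values. Extra table rows by themselves change no estimate. The gain comes from the covariates, which reduce selection bias on observed values and may narrow the interval judged against the margin.

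**What to change.** In the Statistical analysis section:

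1. State that the difference in mean costs and its 95% confidence interval come from a model with baseline AD-SUS cost and baseline HAI as pre-specified covariates. This makes the section agree with the endpoint definition in the Research objectives. The covariates should be fixed in advance and not chosen by whether they turn out to predict availability.
2. State that the same two variables enter any imputation model used for incomplete cases.
3. Add both variables to the comparison of participants with and without service use data, and report that comparison by arm, noting how many lack baseline cost.

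No new data collection is needed. Complete cases have baseline data by definition, so adding baseline cost as a covariate should remove no one from the primary economic sample. The cost is a sentence or two of text, two covariates and a few table rows.

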## Sample size

We calculated sample sizes for both the primary outcome measure and the first secondary outcome measure, choosing the larger of the two for the study.

Based on the pilot study in a genitourinary medicine clinic [10], we assume that the true difference in the change of HAI between CBT and control at 1 year is 5.00 points and that the standard deviation for the change of HAI at 1 year is 7.58 points. With the above assumptions, the study will need 122 patients to detect the above difference with 95% power at a two sided 5% significance level. Taking into account an estimated drop-out rate of 20% drop-out, the sample size is therefore estimated to be 152 patients.

There remains no agreed approach to calculate the sample size required for an economic evaluation, particularly in areas such as health anxiety in which the willingness to pay for improvements in outcomes is unknown. Based on the pilot study, we considered that the CBT intervention would be cost-effective if it improved HAI score and was no more costly than the control treatment. The sample size calculation for the economic evaluation was therefore based on the total costs over 24 months being equivalent.

With a sample size of 186 per group, the study will have 80% power to reject the null hypothesis that the cost of the CBT and control are not equivalent (where the difference in mean costs is +/- £150) in favour of the alternative hypothesis that the means of the two groups are equivalent, assuming the expected difference in means is £0 and the common standard deviation is £580 (from pilot data).

The sample size is thus powered by the first secondary outcome of the CHAMP study, estimated as 466 patients, assuming a 20% drop-out by 24 months, leading to an estimated total of 372 completed with equal randomisation between groups. Thus with 466 patients, or fewer if the drop-out rate is less, the study is adequately powered to both detect the assumed difference in the primary outcome and assess the equivalence in the secondary economic outcome between CBT and control group. The analysis will close on the date on which the last patient has completed the two year follow-up.

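### The cost endpoint is defined as adjusted for baseline, but the £150 equivalence rule names no adjustment, so the estimator that decides equivalence is inconsistent and probably less precise than it could be

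*Protocol article*

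**What the plan says.** Four places in the protocol article bear on the cost comparison.

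- **Research objectives**, hypothesis (ii), defines the endpoint: "the endpoint for this outcome is the cost of health service interventions at 2 years adjusted for baseline values".
- **Sample size** bases the cost calculation on a plain two-group comparison: "With a sample size of 186 per group, the study will have 80% power to reject the null hypothesis" of non-equivalence, "assuming the expected difference in means is £0 and the common standard deviation is £580 (from pilot data"). Nothing marks the £580 as a residual or baseline-adjusted SD.
- **Statistical analysis** gives the estimate: "The difference in mean costs between active treatment and control groups together with the 95% confidence interval will be derived". It then fixes a margin of £150 in advance and sets the decision rule as follows: "The equivalence will be declared between active and control groups in terms of secondary economic outcome if the 95% confidence interval falls within" the limits of minus and plus £150. No covariate is named. Earlier in the same section the HAI model does list the baseline measurement as a covariate.
- **Assessments** confirms that baseline service use is available: "AD-SUS data were recorded at baseline and at 6, 12 and 24 months". The Statistical analysis section also limits the primary economic evaluation to participants with complete data, baseline included.

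**The concern.** The endpoint carries a baseline adjustment where it is defined, and none where it is estimated and judged. An analyst who follows the Statistical analysis section to the letter computes a difference in raw means. One who follows the Research objectives computes an adjusted difference. Under randomisation both target the same mean difference, but they give different point estimates and different interval widths in any one trial, and so can fall on opposite sides of the equivalence rule.

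Two things are at stake. The first is efficiency: if baseline cost is correlated with 24-month cost, the raw comparison gives a wider interval than necessary, in the test that set the trial's size and that has the least power. The second is that an unsettled estimator can be chosen after the data are seen, when the two answers disagree.

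**Working it through.** **Inputs from the documents.** Margin £150, SD £580, true difference £0, 186 per group, stated power 80% (Sample size); 95% confidence interval inside ±£150 (Statistical analysis). **Assumed input.** The correlation r between baseline and 24-month cost, which the documents do not give; values from 0 to 0.7 are shown.

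**Step 1: the plan's own figure.** SE = 580 × √(2/186) = £60.1, and 150/60.1 = 2.494.

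- Equivalence by the 95% interval: power = 2Φ(2.494 − 1.960) − 1 = 2Φ(0.534) − 1 = 40.7%.
- Equivalence by a 90% interval: 2Φ(2.494 − 1.645) − 1 = 60.4%.
- A single one-sided 5% test: Φ(2.494 − 1.645) = 80.2%.

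The stated 80% is reproduced only by the last of these, which is not the rule in the plan. That is a separate matter, but it fixes the starting point: without adjustment, the written rule has about 41% power. By contrast, the HAI comparison (difference 5.00, SD 7.58) has over 99.9% power at 186 per group, so the cost test is the weaker of the two sized in the plan.

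**Step 2: how narrow the rule is.** The 95% half-width is 1.96 × 60.1 = £117.9. Equivalence is declared only if the crude estimate lies within 150 − 117.9 = about £32 of zero.

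**Step 3: effect of adjustment.** Linear adjustment for baseline cost reduces the SD to 580 × √(1 − r²). Then SE = SD × √(2/186) and power = 2Φ(150/SE − 1.960) − 1.

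| r (assumed) | Residual SD (£) | 95% half-width (£) | Power, 95% CI rule |
|---|---|---|---|
| 0 | 580 | 117.9 | 40.7% |
| 0.2 | 568 | 115.5 | 44.2% |
| 0.3 | 553 | 112.5 | 48.7% |
| 0.5 | 502 | 102.1 | 64.2% |
| 0.6 | 464 | 94.3 | 75.3% |
| 0.7 | 414 | 84.2 | 87.5% |

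Solving for 80% power at 186 per group gives r of about 0.64.

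**Step 4: how often the choice changes the answer.** The crude and adjusted estimates differ by chance with SD r × £60.1: £12, £18, £30 and £36 at r = 0.2, 0.3, 0.5 and 0.6. These are not small beside a ±£32 window. In a simulation (normal approximation, true difference £0, SD £580, 186 per group) the two estimators gave different equivalence verdicts in about 11%, 17%, 32% and 41% of trials at those correlations.

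**The case against.** The strongest reply is that there is no contradiction. The Statistical analysis section never calls the cost comparison unadjusted or crude; an adjusted mean difference fits its wording, and the same verb is used for the HAI difference that comes from a baseline-adjusted model. The objectives supply the adjustment and the analysis section supplies the rule. Requiring complete baseline data is consistent with this, although baseline EQ-5D could also explain it. The sentence extending the HAI approach to other assessments could be read the same way, although costs then receive their own separate description. The article is also a condensed text, in which model details may be left to a fuller plan.

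Much of this stands. A reader might infer that the plan commits to an unadjusted analysis; the text does not say so, and silence is the accurate description. A reader might also infer that the plain difference is biased by chance imbalance because randomisation was unstratified. It is not: it is unbiased under randomisation and its interval already allows for chance imbalance. The issue is efficiency.

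The condensation argument does not remove the point. The article chose to state the adjustment, the margin, the interval level and the rule, and it put the adjustment apart from the rule. It names a baseline covariate for the HAI and sizes the cost test on an SD with no allowance for adjustment. Two stated passages are therefore out of step on the estimator.

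**Conclusion.** The point holds as an inconsistency about which estimator is set against £150. On the natural reading of the analysis section, that estimator is less precise than the endpoint in the objectives.

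The size of the loss cannot be fixed from the documents. It is close to nothing if baseline and later cost are weakly related (41% to 44% power at r = 0.2) and large if they are strongly related (64% at r = 0.5, 75% at 0.6). These figures assume a true difference of £0, SD £580, 186 per group, a linear relation and approximate normality of the estimate.

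It would be tempting to blame the missing adjustment for the low power, or to present adjustment as the cure. The documents support neither. The gap between the stated 80% and about 41% comes from the mismatch between the sample size calculation and the 95% interval rule, and exists with or without adjustment. Closing it by adjustment alone would need r of about 0.64 or more.

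**What to change.** In the Statistical analysis section, state that the difference in mean 24-month total cost and its 95% confidence interval come from a regression on the untransformed pound scale with arm and baseline cost as terms; that the ±£150 rule applies to this adjusted estimate; and that the crude difference is reported as supportive. This brings the rule into line with the Research objectives. Further covariates and the method for the interval are matters of preference and are not needed to reconcile the text.

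The cost is a sentence or two. Baseline AD-SUS data are already collected and the complete-case economic set already requires baseline data, so no participant is lost and no new data are needed. The change should be made before cost data are examined by arm.
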